## Abstract

**Background:**

Clinical depression is highly prevalent yet under-detected and under-treated in palliative care settings and is associated with a number of adverse medical and psychological outcomes for patients and their family members. This article presents a study protocol to evaluate a training intervention for non-physician palliative care staff to improve the recognition of depression and provide support for depressed patients and their family members. Details of the hypotheses and expected outcomes, study design, training program development and evaluation measures are described.

**Methods and Design:**

A randomised controlled trial will be implemented across two palliative care services to evaluate the "Training program for professional carers to recognise and manage depression in palliative care settings". Pre-, post- and three-month follow-up data will be collected to assess: the impact of the training on the knowledge, attitudes, self-efficacy and perceived barriers of palliative care staff when working with depression; referral rates for depression; and changes to staff practices. Quantitative and qualitative methods, in the form of self-report questionnaires and interviews with staff and family members, will be used to evaluate the effectiveness of the intervention.

**Discussion:**

This study will determine the effectiveness of an intervention that aims to respond to the urgent need for innovative programs to target depression in the palliative care setting. The expected outcome of this study is the validation of an evidence-based training program to improve staff recognition and appropriate referrals for depression, as well as improve psychosocial support for depressed patients and their family members.

**Trial Registration:**

Australia and New Zealand Clinical Trials Register (ANZCTR): ACTRN12610000183088

## Background

Depression is a significant problem amongst patients receiving palliative care. Studies indicate the prevalence of clinically diagnosable depression in palliative care settings, as defined by the Diagnostic and Statistical Manual of Mental Disorders-IV [1] or International Classification of Diseases-10 [2], is approximately 25 per cent, with up to 50 per cent of patients in this setting reporting high levels of depressive symptomology [3,4]. Factors associated with depression in this population include increased frequency and intensity of physical symptoms, lower general well-being, increased mortality and a hastened desire to die [5-8]. While depression left unaddressed can seriously impact on patients' quality of life, recent evidence supports the efficacy of both pharmacological and psychological treatments in this setting [9,10].

Despite awareness of the high prevalence of depression in this population, rates of detection and treatment are reported to be comparatively low, with only 50 per cent of depressed patients being recognised as depressed and subsequently referred for treatment [11,12]. These low rates of detection strongly indicate the need for improved pathways to care for this vulnerable population. Family members of palliative care patients also represent a high-risk group for psychiatric disorders [13]; yet research indicates they too often do not receive the support needed from professional care services [14,15].

Due to their high level of day-to-day contact with patients, non-physician palliative care staff are in an ideal position to both improve the pathways to care and provide support for depressed patients and their family members. In the project described in this paper, non-physician palliative care staff will participate in a depression training program tailored for the palliative care context as a means to improve their knowledge, attitudes and self-efficacy, and reduce perceived barriers, in regards to detection of depression and the provision of care to depressed patients and their family members. To date, no training program of this type has been evaluated and reported in the scientific literature.

The aim of this paper is to describe the hypotheses of this study, the study design that will be implemented, the development and content of the intervention, and the method of evaluating its efficacy and outcomes.

### Hypotheses and expected outcomes

It is hypothesised that palliative care staff who undertake the depression training program will report higher post-training levels of knowledge, attitudes and self-efficacy and lower perceived barriers in relation to identifying and working with depressed patients compared to pre-training levels and a wait-list control who receive no training. It is also hypothesised that, based on the high prevalence but low detection rates of depression in this context, the number of referrals for depressive symptoms will increase relative to pre-training. The expected outcome of this study is a validated evidence-based program that will assist staff members in recognising depression, increasing appropriate referrals, and improving the care provided for depressed palliative care patients and their family members.

## Methods and design

### Intervention design

The study will constitute a randomised controlled trial, implementing a between-subjects repeated measures design to compare intervention and control conditions over four key areas at three time points. The timeline is outlined in Table 1.

**Table 1 T1:** Evaluation timeline for the Depression Training Program

Evaluation measures for assessing outcomes of the "Training program for professional carers to recognise and manage depression in palliative care settings"	Pre-training	Post-training	3 month follow-up
1. Knowledge of depression	✓	✓	✓
2. View of depression	✓	✓	✓
3. Self-efficacy	✓	✓	✓
4. Barriers to working with depression	✓	✓	✓
5. Number of referrals made for depressive symptoms	✓	✓	✓
6. Family member interviews			✓
7. Staff member interviews			✓

### Target population

The target population will be the non-physician professional care staff that comprise palliative care services. Reflective of the multi-disciplinary nature of these services, and the underlying ideology of active holistic care, health professionals in a broad range of roles will be trained. This will also ensure consistent distribution of information amongst staff and that any gains produced by the training are uniform across the range of services and staff roles. These palliative care staff will be recruited from both in-patient and community palliative care settings.

### Participant groups

A total sample size of 60 was calculated, based on a predicted medium effect size and a statistical power level above 0.8 [16]. Two palliative care services will be recruited into the study with 30 staff from both hospital-based and community based settings recruited from each service. Participants at each site will be randomised to either the intervention condition or the wait-list control condition (no intervention apart from the collection of outcome data). This control group will be offered the training following completion of the study. All attempts will be made to ensure that the sample size and the distribution of participants' professional discipline within the palliative care team (e.g. nursing, occupational therapy, etc.) will be even across sites and conditions.

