• diagnostic definitions and prevalence • signs and symptoms of depression useful for detection in the palliative care setting • distinguishing grief and depression • impact on physical, psychological and social areas at end-of-life • treatments • common misconceptions • distinguishing depression and anxiety	• using a depression monitoring checklist [17,18] * • communication skills • factors related to masked depression in palliative care settings • barriers to detection of depression in palliative care settings	• using a two-question depression screening tool [19,20] ** • responding to depression-related and 'desire to die' statements • support strategies for depressed patients	• psychological distress amongst patient's family members • the family system • support strategies for family members of patients • grief and bereavement • cultural considerations • self-care strategies for staff

*This depression monitoring checklist has been adapted from a similar checklist that has demonstrated success in the aged-care setting in assisting staff to recognise depression **This screening tool specifically targets clinical depression, has been validated against reliable and valid measures of depression, and has demonstrated good psychometric properties in the palliative care setting.

The intervention is designed to be delivered in four 90-minute sessions over the course of four consecutive weeks. This format was chosen so as to allow participants to engage in simple homework tasks between sessions to facilitate the transfer of learned skills to daily practice, for example, trialling methods of detecting depression or implementing support strategies. The outcomes of set homework tasks will be discussed in a group format at the start of sessions two, three and four, so feedback can be given and any questions or issues addressed. Group discussions such as these will be encouraged throughout the program to complement the individual and group activity worksheets used alongside information delivered didactically in a lecture-style format. This dynamic format has been chosen to encourage both the learning of the program content and the sharing of experiences and perspectives amongst palliative care staff in diverse roles.

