A presenter's manual and slide presentation has been developed and will be accompanied by a training support kit for participants that includes worksheets, a copy of the slide presentation, and information on resources to provide to depressed patients and family members.

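### Randomising individual staff within two shared services exposes wait-list controls to the training, and the article describes no step to limit this and no measure to record it

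*Protocol article*

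**What the plan says.** **Allocation.** In the Participant groups section, "Two palliative care services will be recruited into the study with 30 staff from both hospital-based and community based settings recruited from each service". Within each service the unit randomised is the individual: "Participants at each site will be randomised to either the intervention condition or the wait-list control condition (no intervention apart from the collection of outcome". The section adds that every attempt will be made to see that numbers and professional disciplines "will be even across sites and conditions". Controls are offered the training only once the study is over.

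**What trained staff carry into the workplace.** The Intervention Program section describes four weekly sessions with "simple homework tasks between sessions to facilitate the transfer of learned skills to daily practice, for example, trialling methods of detecting depression or implementing support". It also describes what trained staff are given: "training support kit for participants that includes worksheets, a copy of the slide presentation, and information on resources to provide to depressed patients and family". Table 2 includes a checklist for monitoring depression and a two-question screen.

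**What is measured.** Table 1 lists four staff questionnaires and referral counts at pre-training, post-training and three months, and interviews of family members and staff at three months. The staff interviews are for those who took part in the training.

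**Sample size.** "A total sample size of 60 was calculated, based on a predicted medium effect size and a statistical power level above 0.8".

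**Referrals.** The section on patients and their family members says that referral rates come from facilities of two kinds, intervention and control.

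**The concern.** The training is easy to pass on. It consists of information, a slide set, worksheets, a checklist and a short screen, and trained staff are asked to use the methods at work between sessions. The four staff outcomes (knowledge, attitudes, self-efficacy and perceived barriers) are ones that a colleague can influence. Because trained and untrained staff belong to the same service, with disciplines balanced between them, some of the effect may reach the control arm.

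That would shrink the between-arm difference, and the three-month comparison would be the most exposed. None of the listed measures asks controls what they saw or heard, and the staff interviews leave controls out. A small or null difference would then be hard to interpret: the training may have done little, or part of its effect may have been shared. Exposure that is not recorded during the trial cannot be reliably recovered afterwards.

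**Working it through.** **Inputs from the article.** Two services; 30 staff each; total 60; an even split intended; power above 0.8 for a medium effect; four weeks of training; last outcome at three months.

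**Assumed, because the article does not give them.** Two-sided 5% level, no dropout, and a sharing fraction c (the share of the training effect that reaches controls). The article gives no value for c, so a range is shown.

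**Step 1: exposure.** 30 / 2 = 15 per arm per service. Four weeks + three months = about four months from the first session to the last outcome.

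**Step 2: the stated 60.** No standard calculation tried returns exactly 60 for power 0.80:

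- Plain two-group comparison, d = 0.5: 63 per arm, 126 in total (128 by the exact t-test).
- Baseline-adjusted comparison, d = 0.5: 96, 66 or 46 for baseline correlation 0.5, 0.7 or 0.8.
- Repeated-measures group-by-time interaction, f = 0.25, three times: 53, 38 or 28 for within-person correlation 0, 0.3 or 0.5.
- Repeated-measures between-group effect, f = 0.25: 44, 69 or 86 for the same correlations.
- Four outcomes jointly (Hotelling): 53 at f² = 0.25, 85 at f² = 0.15.

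Several of these give power above 0.8 at 60. The article does not say which was used, so the figure can be neither confirmed nor called wrong. It is taken as stated, at its floor of 0.80.

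**Step 3: dilution from the stated power.** If controls gain a fraction c of the effect, the difference falls to (1 − c) of its size. By the normal approximation:

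power = Φ[(1.960 + 0.842)(1 − c) − 1.960], and the N that restores 0.80 is 60 / (1 − c)².

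For c = 0.20: 2.802 × 0.80 − 1.960 = 0.281, and Φ(0.281) = 0.61; 60 / 0.64 = 93.75, so 94.

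**Step 4: the same under a repeated-measures reading.** The group-by-time test for one outcome stands in for the planned repeated-measures MANOVA: f = 0.25(1 − c), m = 3 times, N = 60, noncentrality N·m·f² / (1 − ρ), degrees of freedom 2 and 116. At c = 0 the noncentrality is 60 × 3 × 0.0625 = 11.25 for ρ = 0 and 22.5 for ρ = 0.5.

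| Sharing c | Power from stated 0.80 | N to restore 0.80 | Interaction, ρ = 0 | ρ = 0.3 | ρ = 0.5 |
|---|---|---|---|---|---|
| 0 | 0.80 | 60 | 0.85 | 0.95 | 0.99 |
| 10% | 0.71 | 75 | 0.77 | 0.90 | 0.97 |
| 20% | 0.61 | 94 | 0.66 | 0.82 | 0.93 |
| 30% | 0.50 | 123 | 0.54 | 0.70 | 0.84 |
| 50% | 0.29 | 240 | 0.30 | 0.41 | 0.54 |

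**Step 5: the two descriptions of the control.** The Participant groups section puts both arms inside each site. The referral text treats whole facilities as intervention or control. Both cannot describe the same allocation. If arms sit within services, a count taken per facility cannot be split by arm. If whole services were allocated, sharing would be much smaller, but with only two services the arm would be confounded with the site. The Participant groups section is the explicit statement of randomisation, and its aim of evenness across both sites and conditions supports the within-site reading used here.

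**The case against.** **The article is a condensed text.** A non-sharing request or extra questionnaire items could sit in the full protocol or the study materials. That is fair, and the point is limited to what this article describes. But the article does fix the within-service allocation, the portable materials and the list of measures, and a risk follows from these as written.

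**Contamination is not demonstrated.** This stands. Each service spans hospital and community settings, so a given trained and untrained pair need not work together. Part of the programme is group work and feedback, which cannot be handed over like a slide set. Sharing is a plausible risk of unknown size.

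**Control scores are observed three times.** Flat scores in both arms would argue against a shared effect. A rise among controls would be a signal, but one that cannot be told from the effect of retesting. Control scores alone therefore do not measure exposure.

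**Three stronger readings are tempting and are not supported.**

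- A reader might infer that the Target population section plans for spill-over, since it says "This will also ensure consistent distribution of information amongst staff and that any gains produced by the training are uniform across the range of services". Its subject is the preceding sentence, on training a broad range of roles. It says nothing about untrained staff and does not contradict the definition of the control.
- A reader might start from a plain two-group test at d = 0.5 with 30 per arm, where power is 0.48 and falls to 0.33, 0.27 or 0.16 with 20%, 30% or 50% sharing. The arithmetic is right, but that is one outcome at one visit. The Data analysis section plans a repeated-measures MANOVA, and the article states power above 0.8 without the inputs needed to refute it.
- A reader might call the observed difference a lower bound on the training effect. Outcomes are self-reported and wait-list staff know that they are untrained, which can push the difference upward. The net direction is not known.

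**Conclusion.** The concern holds as a design risk that the article leaves open. Randomising individuals within two services, with portable materials and practice at work over about four months, makes some exposure of controls likely enough to plan for. Taken alone, that exposure would bias the between-arm difference towards no effect. The article describes nothing to limit it, and its listed measures would not show it.

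The size is conditional on the sharing fraction, which is assumed throughout, and on power inputs that the article does not state. From the stated power at its floor of 0.80, a fifth of the effect shared costs about 0.19 (0.80 to 0.61) and a half costs about 0.51 (0.80 to 0.29). Under a favourable repeated-measures reading (ρ = 0.5), power stays above 0.80 up to 30% sharing and falls to 0.54 at 50%. The result does not show that the trial is underpowered or that sharing will occur. It supports a cheap improvement in conduct, and it requires the two descriptions of the control to be reconciled.

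**What to change.** Keep randomisation within sites, since two services are too few to randomise whole services. Then:

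1. At consent, ask trained staff not to pass the kit, slides, worksheets or checklist to untrained study colleagues until the three-month data are collected. State plainly that this does not restrict any communication about patients' care.
2. Add two or three items to the post-training and three-month questionnaires of both arms, asking whether the respondent has seen the training materials or has discussed the sessions with a trained colleague.
3. Report control exposure descriptively by time point and site. Label any analysis by exposure as exploratory, because exposure is self-selected and arises after randomisation. Do not present the between-arm difference as a lower bound.
4. Reconcile the referral text with the Participant groups section, and say how referrals are attributed to an arm.

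The cost is a sentence at consent, a slightly longer questionnaire and a temporary limit on sharing training materials. No extra participants are needed. If the full protocol already contains items 1 and 2, a sentence in the article saying so would be enough for those two.

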### Intervention Program: "Training program for professional carers to recognise and manage depression in palliative care settings"

The depression training program, titled "Training program for professional carers to recognise and manage depression in palliative care settings", was developed by drawing from the researchers' experience with depression training in the aged care setting [17,18] and subsequently adapting this framework to the palliative care setting. A literature review pertaining to depression and psychosocial care in palliative care settings was conducted, and information relevant to the objectives of the study was extracted. This evidence-based information was then used to inform the content of the training program. In addition to the literature review, a needs analysis was also conducted which involved focus group interviews with managerial palliative care staff, non-managerial palliative care staff, and family members of patients currently receiving palliative care. These interviews were thematically analysed and information relating to staff knowledge, attitudes, self-efficacy and perceived barriers to depression detection and care provision were extracted and used to further inform the development of the training program. The final program consisted of four sessions focussing on the following main topics: Understanding depression, detecting depression, responding to depression and a focus on the patient's family members. These sessions integrated factual information about depression in palliative care settings (such as its effects or treatment approaches to depression), depression-related and mental health service provision issues unique to this setting (such as distinguishing grief from depression or how depression might be masked), validated approaches to the detection of depression in palliative care (such as a two-question screening tool), and context-specific provision of care for depressed patients and their family members (such as psychosocial care strategies). The specific content of the training program is outlined in Table 2.

**Table 2 T2:** Delivery format and content of the "Training program for professional carers to recognise and manage depression in palliative care settings"

Session 1 Understanding Depression	Session 2 Detecting Depression	Session 3 Responding to Depression	Session 4 Family Focus
• diagnostic definitions and prevalence • signs and symptoms of depression useful for detection in the palliative care setting • distinguishing grief and depression • impact on physical, psychological and social areas at end-of-life • treatments • common misconceptions • distinguishing depression and anxiety	• using a depression monitoring checklist [17,18] * • communication skills • factors related to masked depression in palliative care settings • barriers to detection of depression in palliative care settings	• using a two-question depression screening tool [19,20] ** • responding to depression-related and 'desire to die' statements • support strategies for depressed patients	• psychological distress amongst patient's family members • the family system • support strategies for family members of patients • grief and bereavement • cultural considerations • self-care strategies for staff

*This depression monitoring checklist has been adapted from a similar checklist that has demonstrated success in the aged-care setting in assisting staff to recognise depression **This screening tool specifically targets clinical depression, has been validated against reliable and valid measures of depression, and has demonstrated good psychometric properties in the palliative care setting.

The intervention is designed to be delivered in four 90-minute sessions over the course of four consecutive weeks. This format was chosen so as to allow participants to engage in simple homework tasks between sessions to facilitate the transfer of learned skills to daily practice, for example, trialling methods of detecting depression or implementing support strategies. The outcomes of set homework tasks will be discussed in a group format at the start of sessions two, three and four, so feedback can be given and any questions or issues addressed. Group discussions such as these will be encouraged throughout the program to complement the individual and group activity worksheets used alongside information delivered didactically in a lecture-style format. This dynamic format has been chosen to encourage both the learning of the program content and the sharing of experiences and perspectives amongst palliative care staff in diverse roles.

A presenter's manual and slide presentation has been developed and will be accompanied by a training support kit for participants that includes worksheets, a copy of the slide presentation, and information on resources to provide to depressed patients and family members.

